# Effects of high-intensity interval training on depressive symptoms in Hong Kong community-dwelling older adults with mild to moderate depressive symptoms: a study protocol for a cluster randomized controlled trial

**DOI:** 10.3389/fpubh.2026.1697763

**Published:** 2026-01-27

**Keywords:** Baduanjin Qigong, community dwelling, depressive symproms, high-intensity interval training, older adults

## Abstract

**Background:**

Older adults with mild to moderate depressive symptoms are at high risk of developing severe depression along with complications, disability, and mortality. Early intervention during mild to moderate stages of depressive symptoms is important to prevent further deterioration. Exercise as a readily available approach has been recognised for reducing depressive symptoms. High-intensity interval training (HIIT), a novel form of exercise that has the potential to improve both depressive symptoms and physical health, has garnered increasing attention. However, the application of HIIT to address depressive symptoms among older adults remains scarce.

**Aims:**

This proposed study aims to investigate the effects of HIIT on depressive symptoms, biomarkers of depressive symptoms, physical fitness, sleep quality, and quality of life in Hong Kong community-dwelling older adults with mild to moderate depressive symptoms.

**Methods:**

This study will be a single-blinded, cluster-randomised, controlled trial comprising three groups and three assessments. The three groups will consist of a HIIT group, a Baduanjin Qigong control group, and a recreation workshop non-exercise control group. The 144 eligible participants from 9 community centres (clusters) will be randomly allocated in a 1:1:1 ratio to three groups for 16 weeks through cluster randomisation. The primary outcome measure will be self-reported depressive symptoms. The secondary outcome measures will include salivary cortisol (a biomarker of depressive symptoms), physical fitness, sleep quality, and quality of life. The outcomes will be assessed at baseline, after completion of the intervention, and at a three-month follow-up.

**Discussion:**

This study will provide valuable evidence on whether older adults in the HIIT group could gain more improvement in depressive symptoms and other health-related benefits compared to the control groups. If HIIT demonstrates superiority, it could be prescribed as a new exercise regimen to benefit older adults with depressive symptoms in future studies. The research findings may have considerable impacts on the future prevention and treatment of mental disorders and may also contribute to promoting healthy aging among Hong Kong older adults.

**Clinical trial registration:**

ClinicalTrials.gov, identifier NCT06014294.

## Introduction

1

Depressive symptoms are a common mental health problem and contribute to morbidity and mortality in ageing populations (1–3). Previous studies have indicated a high prevalence of depressive symptoms in older adults globally (31.7%) (4). The values are greater in the Hong Kong population (32.3%) (5). Depressed older adults present with a series of common symptoms, including depressed mood, insomnia, vague somatic pains, and cognitive decline (6). Older adults with depressive symptoms often experience chronic illnesses, reduced fitness, poor sleep quality, and a decline in quality of life (7–9). Furthermore, these individuals frequently exhibit abnormal hormone patterns, particularly concerning cortisol, which may negatively impact their cognitive function and physical health (10). Those experiencing clinical depression or non-clinical depressive symptoms have been found to have a blunted cortisol awakening response or overall lower cortisol levels (11, 12). Cortisol has been proposed as a potential biomarker of both major depressive disorder and depressive symptoms in the context (12, 13). Depressive symptoms can be categorised as mild, moderate, and severe (14). Compared to people with mild to moderate depressive symptoms, those with severe conditions may develop psychotic symptoms (e.g., delusions) and have higher mortality, disability, and treatment costs (15). Effective interventions for mild to moderate depressive symptoms can prevent the deterioration of depressive pathology to severe and psychotic symptoms. Therefore, addressing this issue while considering personal, social, and economic factors for public health is particularly urgent.

Exercise has been extensively recommended as an alternative way to improve depressive symptoms among older adults (16). In addition to providing antidepressant effects similar to other approaches (pharmacological interventions, psychotherapy) (17, 18), exercise can offer substantial concurrent benefits, such as ameliorating chronic disease, increasing physical fitness, improving sleep quality, and improving quality of life (19–22). Further, exercise is cost-effective and can be offered to larger populations as it has fewer contraindications. In previous research, mind–body exercise (e.g., Baduanjin Qigong, Tai Chi, Yoga) has emerged as a compelling recommendation for improving depressive symptoms among older adults when compared with aerobic exercise, strength training, multi-component exercise, and exergaming (23–25). Four meta-reviews have indicated that mind–body exercise typically involves low to moderate intensity and longer durations, emphasising slow movements, breath regulation, and achieving mind–body balance (23–26). However, the long duration (≥ 60 min/session in most mind–body exercises) (26), slow pace, and cognitive demand may discourage depressed older adults from maintaining the interventions (26–28). Although studies have recommended low-intensity mind–body exercise for health benefits with high adherence among older adults, evidence has shown that high-intensity exercise can yield more improvement in depressive symptoms and physical function after exercise intervention, especially for older adults with depression (29–31).

High-intensity interval training (HIIT) is an increasingly popular exercise modality that includes repeated bouts of high-intensity exercise, typically lasting seconds to minutes, interspersed with rest periods (32). Recent research has demonstrated the potential antidepressant effects of HIIT interventions by modulating brain-derived neurotrophins, dopamine, and the homeostasis of the HPA axis, through enhanced cardiovascular and cerebrovascular function. This suggests a biological mechanism for HIIT interventions in the prevention and treatment of depressive symptoms (33). Psychologically, accomplishing short intensive workouts can alleviate depressive symptoms by helping individuals divert from rumination and fostering a sense of mastery, self-efficacy, and resilience (34–37). Moreover, HIIT appears to be a promising approach showing greater effects on cardiorespiratory function and physical fitness than low to moderate-intensity exercise (38). In addition, a scoping review of HIIT programs among older adults found that HIIT was generally safe, well-tolerated, and associated with high adherence (31).

Over the past 20 years, most HIIT research has focused on adolescents (39, 40), adults (32, 41), healthy older adults and older adults with heart disease (31, 42). No previous HIIT study has investigated older adults with mild to moderate depressive symptoms. In addition, some studies have demonstrated methodological weaknesses, including inadequate control groups for exercise, small sample sizes (from 11 to 38 participants in the HIIT group) (41, 43, 44). Additionally, most HIIT programs have been conducted in a laboratory environment, and depressive symptoms were only examined as a secondary outcome. These research findings may limit the evaluation and application of HIIT interventions on depressive symptoms when generalising to a real-world setting. Therefore, there is an urgent need to investigate the efficacy of HIIT on depressive symptoms and whether it can yield superior effects compared to mind–body exercise and a non-exercising control group among older adults in community settings.

The current study aims to evaluate the effectiveness of a HIIT intervention program on depressive symptoms among Hong Kong older adults with mild to moderate depressive symptoms compared with Baduanjin Qigong and a non-exercise control. The following Hypotheses will be tested in this study: (1) participants in the exercise groups (HIIT group; Baduanjin Qigong group) would have greater improvements in self-reported depressive symptoms, a biomarker of depressive symptoms (salivary cortisol), physical fitness, sleep quality, and quality of life than the non-exercise control group (recreation workshop group) at post-intervention and 3 months after the intervention; (2) participants in the HIIT group would have greater improvements in self-reported depressive symptoms, biomarker of depressive symptoms (salivary cortisol), physical fitness, sleep quality, and quality of life than the Baduanjin Qigong control group at post-intervention and 3 months after intervention.

## Methods

2

The study protocol was approved by the Ethics Committee of Hong Kong Baptist University (approval number: REC/21–22/0169). The trial will comply with the Helsinki Declaration and the international Good Clinical Practice Guidelines (45). A written informed consent form will be collected from each participant. Personal information about potential and enrolled participants will be protected confidentially.

### Study design

2.1

This study will be a single-blinded three-group cluster-RCT to examine the effects of HIIT intervention on depression symptoms, physical fitness, sleep quality, and quality of life immediately after a 16-week intervention and the residual effects 3 months following completion of the intervention. A cluster random sampling method will be adopted to recruit the participants. With elderly centres used as a cluster unit for randomization and intervention, nine elderly centres in Hong Kong will be randomly assigned to three groups. Thus, participants will be randomly recruited and assigned through elder centres to one of three groups: a HIIT group, an exercise control group (Baduanjin Qigong), and a non-exercise control group (recreation workshops). Randomisation will be conducted using the random function available in Excel by a researcher who will not be involved in the participant recruitment and data collection. The block size for randomization will be 3, and the clusters within each block will be sorted by block number and a random number. Evaluation will be conducted at pre-intervention (T1), post-intervention (T2), and 3 months after intervention completion (T3). Outcome assessors will be blinded to the intervention assignment results. The CONSORT flow diagram (46) is presented in Figure 1.

**Figure 1 fig1:**
[figure not shown]
Consort flow diagram.

### Study participants

2.2

The target participants will be community-dwelling older adults with mild to moderate depressive symptoms in Hong Kong. The following selection criteria will be employed to screen for eligibility: (1) 60 to 74 years at the start date of the project; (2) Chinese version of Geriatric Depression Scale (GDS-15) scoring 5–11 (i.e., mild to moderate level of depressive symptoms) (47); (3) pass the PAR-Q + screening (48) or with the physician’s approval for readiness of participation in the high-intensity exercise; (4) no severe chronic diseases, such as coronary heart disease, chronic heart failure, chronic obstructive pulmonary disease, osteoarthritis, which are diagnosed clinically in the medical history; (5) reach the average level of 2-min step test (aerobic fitness; ≥ 94 counts for male and female), 30 s sit and stand (lower limb strength; ≥ 15 counts 94 for male and female), and the timed up and go fitness test (mobility and dynamic balance; ≤ 5.9 s for male and female) showing physical competence for high-intensity exercise, based on the fitness norm of Chinese community-dwelling older adults (49); (6) no cognitive impairment, as determined by the Chinese version of the Mini-Mental Status Examination (i.e., score ≥ 24) (50); (7) No previous substantial experience in practicing HIIT or Baduanjin Qigong. A signed written informed consent form will be collected from each participant.

### Sample size estimation

2.3

According to government data, each neighbourhood elderly centre in Hong Kong must have at least 800 members per year (Social Welfare Department, https://www.swd.gov.hk/). All these conditions enable us to recruit sufficient older adults with mild and moderate levels of depressive symptoms to the centre. Hence, for a feasible study implementation principle, a cluster size of 16 was selected in the current study. An average medium effect size (Cohen’s *f* = 0.25 converted from *η*^2^ = 0.06) based on previous meta-analysis studies with HIIT interventions on depression (51), an alpha of 0.05, a statistical power of 90%, an ICC of 0.01, and a 30% attrition rate (43) are the parameters of the estimation. Sample size was calculated by G*Power 3.1.9.7 software, using repeated measures to detect the within-between interaction between ANOVA analyses of three assessments by three groups, and equation for cluster design = [1 + (n-1)*ρ*], *n* is the average cluster size, *ρ* is the intraclass correlation coefficient, which represents the correlation between observations within the same cluster (52). A total of 144 participants in 9 clusters (3 clusters with 48 participants each) will be required for this study.

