### Data analysis

2.9

All data analyses will be conducted using SPSS version 29. Descriptive statistics will be used to describe the baseline characteristics of participants. The primary analyses will use intention-to-treat analysis involving all randomised participants at baseline (77). Missing data from both dropouts and completers will be imputed using a multiple imputation (MI) approach with chained equations before the analysis (78). Further, generalised linear mixed models (GLMM) will be applied to evaluate the intervention effects on outcome measures at baseline, post-intervention, and follow-up, with time, groups, and their interaction as fixed effects. The baseline values showing significant differences across groups will be controlled as covariates, while elderly clusters and individuals will be treated as random effects. *Post-hoc* tests will be conducted if a significant interaction effect is detected using the sequential Sidak method for multiple comparisons. The intra-class correlation coefficient (ICC) will be calculated to identify the variance between elderly centres. The significance level will be set as 95% (two-tailed), and the effect size Cohen’s *d* will be calculated for within and between groups, where *d* = 0.30, 0.50, 0.80, indicating a small, medium, and large effect size, respectively.

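### The 90% power in section 2.3 is not power for a medium between-arm difference: on the G*Power scale that reproduces 144, f = 0.25 for the 3 × 3 interaction means 1.1 to 1.3 SD, and 0.5 SD has about 20% to 74% power

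*Protocol article*

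**What the plan says.** Section 2.3 (Sample size estimation) of the protocol article starts from "An average medium effect size (Cohen’s *f* = 0.25 converted from *η*^2^ = 0.06", attributed to earlier meta-analyses of HIIT and depression. The other parameters are "an alpha of 0.05, a statistical power of 90%, an ICC of 0.01, and a 30% attrition rate". The test is fixed by "using repeated measures to detect the within-between interaction between ANOVA analyses of three assessments by three groups", and "Sample size was calculated by G*Power 3.1.9.7 software". Clustering enters through the "equation for cluster design = [1 + (n-1)*ρ" factor, and "a cluster size of 16 was selected in the current study". The result is 144 participants in nine centres, 48 per arm. The section gives neither the correlation between repeated measurements nor the G*Power effect-size option, and it does not express the target as a between-arm difference in GDS points or SD.

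Section 2.9 (Data analysis) lists Cohen's d of 0.30, 0.50 and 0.80 as "indicating a small, medium, and large effect size, respectively". It plans post-hoc comparisons with a sequential Sidak adjustment if the interaction is significant.

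The Introduction states the hypotheses as arm-to-arm claims. The second is that "participants in the HIIT group would have greater improvements in self-reported depressive symptoms" than the Baduanjin group, among other outcomes.

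**The concern.** An eta-squared of 0.06 (f = 0.25) is the usual medium effect for a comparison of group means; with two equal groups f = d/2, so it corresponds to d = 0.5. The same number does not keep that meaning when it is entered for a group-by-time interaction. On G*Power's default scale, f is then the root mean square of the nine interaction residuals divided by the SD within a cell. A between-arm difference in change is spread over nine cells, so a much larger difference is needed to reach f = 0.25.

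A reader who sees a medium effect and 90% power together will take the trial to be well powered for d = 0.5. A null result, above all for HIIT versus Baduanjin, could then be read as good evidence of no difference when the trial had little chance of showing one.

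**Working it through.** **Inputs.** From section 2.3: f = 0.25, alpha 0.05, power 90%, ICC 0.01, cluster size 16, attrition 30%, three arms, three assessments, N = 144. From section 2.9: two-sided tests, d = 0.50 as medium. Assumed because not stated: the repeated-measures correlation ρ (shown from 0 to 0.7) and the G*Power option. SDs are cross-sectional. The article gives no GDS SD, so nothing is converted to points.

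**1. Reproducing 144.** The default option uses λ = f² × N × 3 / (1 − ρ), with 4 and 2(N − 3) df.

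- Design effect: 1 + (16 − 1) × 0.01 = 1.15.
- ρ = 0: 90% power needs N = 85, or 87 with equal arms. 87 × 1.15 / 0.7 = 142.9, hence nine clusters of 16 = 144.
- ρ = 0.3: N = 60. 60 × 1.15 / 0.7 = 98.6. With equal whole clusters of 16 per arm, totals go 48, 96, 144, so this also becomes 144. The same holds up to ρ of about 0.32.
- ρ = 0.5: N = 45. 45 × 1.15 / 0.7 = 73.9, which would give 96.
- The other two options give 129 × 1.15 / 0.7 = 211.9 (SPSS) and 126 × 1.15 / 0.7 = 207.0 (Cohen). The Cohen option comes near 144 only if attrition is left out: 126 × 1.15 = 144.9.

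The default option with ρ between 0 and about 0.32 is therefore the only route tried that uses every stated input and gives 144.

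**2. What f = 0.25 means on that scale.** Take equal baselines and a difference in change d held at T2 and T3. The time pattern (−2/3, 1/3, 1/3) has sum of squares 2/3.

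- One arm differs: arm pattern (−1/3, −1/3, 2/3), sum of squares 2/3. f = d × √[(2/3 × 2/3) / 9] = 0.2222 d, so d = 0.25 / 0.2222 = 1.125.
- Baduanjin halfway: arm pattern (−1/2, 0, 1/2), sum of squares 1/2. f = d × √[(1/2 × 2/3) / 9] = 0.1925 d, so d = 0.25 / 0.1925 = 1.30.

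**3. Interaction-test power for a true largest difference of 0.5 SD.** Here f = 0.5 × 0.1925 = 0.096 or 0.5 × 0.2222 = 0.111. Effective N = 144 × 0.7 / 1.15 = 87.7. The last two columns replace the denominator df by a centre-based 2 × (9 − 3) = 12.

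| ρ | Baduanjin halfway | One arm differs | Halfway, 12 df | One arm, 12 df |
|---|---|---|---|---|
| 0 | 20% | 26% | 15% | 19% |
| 0.3 | 27% | 36% | 20% | 26% |
| 0.5 | 38% | 49% | 27% | 36% |
| 0.7 | 60% | 74% | 44% | 57% |

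With no attrition (effective N 144 / 1.15 = 125) and individual-level df, ρ = 0.7 gives 78% and 89.5%. That is the best case in the range.

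**4. Arm-to-arm contrasts.** Effective n per arm = 87.7 / 3 = 29.2. For change scores SE = √[4(1 − ρ) / 29.2], which is 0.262 SD at ρ = 0.5. Noncentral t, two-sided 0.05, no multiplicity adjustment:

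- HIIT versus workshop at 0.5 SD: 0.5 / 0.262 = 1.91, power about 47%, or 36% with 9 − 3 = 6 centre-based df.
- HIIT versus Baduanjin at 0.25 SD: power about 16%, or 13% with 6 df.
- Detectable difference at 80% power: about 0.75 SD with individual-level df, 0.88 SD with 6 df.

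**The case against.** **The arithmetic is sound.** This stands. The design effect is right, 144 reproduces, and the 90% is correct for f = 0.25 on the default scale. The fault lies in what f = 0.25 is taken to mean.

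**Zero correlation.** A reader might infer that 144 can only come from assuming uncorrelated repeated measures. It cannot be inferred: with equal whole clusters per arm, any correlation from 0 to about 0.32 gives 144.

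**Nine centres.** A reader might also infer that centre-based df pull the planned power at f = 0.25 down to 77%. That is the correlation-0 case only; at 0.3, which also gives 144, the figure is 91%. The analysis does model centre as a random effect, and the df method is commonly left to the analysis plan.

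**The option is unstated and the meta-analysis is not at hand.** This makes the 1.1 to 1.3 SD figure conditional. Under the Cohen option with attrition forgotten, f = 0.25 would mean 0.65–0.75 SD at correlation 0.5, or 0.92–1.06 SD at 0, and the stated attrition would leave about 75% power. The power for a true 0.5 SD in steps 3 and 4 does not depend on the option.

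**Testing the interaction first fits the analysis.** It does, since the post-hoc tests follow only a significant interaction. But the hypotheses are about pairs of arms, and the 90% says nothing about those. The d thresholds in section 2.9 are for reporting results, yet they are the article's own statement of what medium means.

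**Conclusion.** The point holds as a mismatch of effect-size scale. On the default G*Power scale, the only one tried that yields 144 from all stated inputs, the trial is sized for a sustained difference in change of 1.125 to 1.30 SD, above even the 0.80 that section 2.9 calls large. For a largest difference of 0.5 SD, interaction-test power after the planned attrition is 20% to 74% over correlations of 0 to 0.7 and the two effect patterns, and lower if df reflect nine centres. It stays below 90% in that range even with no attrition. The arm-to-arm contrasts that the hypotheses need are weakest for HIIT versus Baduanjin.

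These figures assume equal baselines, an effect held to T3, a cross-sectional SD, and the article's ICC and attrition. The documents do not support saying that the sample size is miscalculated or that 144 must be raised.

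**What to change.** Keep 144 and restate section 2.3:

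- Name the G*Power effect-size option and the assumed repeated-measures correlation.
- State the between-arm difference in GDS change, in SD or points, that f = 0.25 represents, and stop presenting the 90% as power for a medium effect.
- For the HIIT–workshop and HIIT–Baduanjin GDS contrasts, report power or the minimum detectable difference over a range of correlations with centre-based df. The 0.75 SD and 0.88 SD above are an example. They rest on correlation 0.5, an assumed value that does not itself lead to 144 on the default scale.
- Say plainly that HIIT versus Baduanjin does not have 90% power for a medium difference.

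The cost is wording only, with no extra participants and no change of analysis. The downside is that the stated power becomes less favourable.

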### Intervention content

2.4

#### Intervention group (High-Intensity Interval Training, HIIT)

2.4.1

Based on previous literature, the duration of effective HIIT programs for improving mental and physical health among older adults generally ranges from 4 to 16 weeks, with at least two sessions per week (31, 51). Considering that people with depressive symptoms may need more time to obtain benefits from exercise therapies, as well as the feasibility of program implementation in older adults, an intervention period of 16 weeks with two sessions per week (a total of 32 training sessions) will be adopted in the current intervention. Each session will comprise three sections: warm-up, main exercise, and cool-down.

According to the HIIT recommendations formulated by the American College of Sports Medicine (53), the intensity of HIIT workouts will be designed at 80–90% HRmax (Borg categorical scale 5–9) to ensure safety and maximum benefit for older adults. HRmax is estimated via an age-related prediction equation [HRmax = 208-(0.7*age)] (54). Exercise intensity will be monitored by heart rate monitors (Polar Verity Sense) as well as self-reported Rate of Perceived Exertion (RPE) using a Borg categorical scale of 0–10 (55, 56). For Week 1–2, the HIIT section will include ten intervals of 30 s of HIIT work at 80–90% HRmax (RPE 5–9), separated by nine intervals of 60 s of active recovery at 50–70% HRmax (RPE 1–3). For warm-up and cool-down sections, the intensity will be set as 50–70% HRmax (RPE 1–3). The workloads of each HIIT interval will be increased by 5 s every two weeks and finally reach 19 min 45 s in Week 15–16. The total HIIT section will progress from 14 min in Weeks 1–2 to 19 min 50 s in Weeks 15–16. Given that diverse types of exercise may contribute more to the improvement of depressive symptoms compared with only a single type of exercise (57). Each HIIT section will include 10 movements of aerobic and resistance combined exercises, where each movement will be performed as quickly as possible within one interval. There is a total of 38 different movements in the HIIT program. The HIIT program will be guided by a qualified instructor from the Physical Fitness Association of Hong Kong with the assistance of student helpers. The content for the formal HIIT program is presented in Table 1.

**Table 1 tab1:** Intervention content of HIIT.

HIIT 2 sessions/week	Warm-up	HIIT section		Cool-down
Intensity	50–70% HRmax (1–3 RPE)	HIIT work intervals: 80–90% HRmax (5–8 RPE) Recovery intervals: 60–70% HRmax (2–3 RPE)		50–70% HRmax (1–3 RPE)
Week 1–2	10-min: stretching and dynamic movement	14 min 30 s HIIT work x 10 intervals + 60 s active recovery x 9 intervals	HIIT work (10 movements) (1) lunge with fast punch; (2) squat with calf raise; (3) rope skipping; (4) standing crunch; (5) star jumping; (6) straight leg touch; (7) butt kickers; (8) sumo squat and side crunch; (9) running; (10) high knees and claps. Active recovery: Step-on	10-min: Light walking, stretching, abdominal breathing, and relaxation
Week 3–4		14 min 50 s 35 s HIIT work x 10 intervals + 60 s active recovery x 9 intervals	HIIT work (10 movements) (1) *squat with a fast punch*; (2) squat with calf raise; (3) rope jump; (4) *standing side crunch*; (5) star jumping; (6) straight leg touch; (7) butt kickers; (8) *squat to front kick*; (9) running; (10) *squat with lunge*. Active recovery: Step-on	
Week 5–6		15 min 40 s 40 s HIIT work x 10 intervals + 60 s active recovery x 9 intervals	HIIT work (10 movements) (1) squat with fast punch; (2) *squat twist*; (3) *scissor jumps*; (4) standing crunch; (5) star jumping; (6) straight leg touch; (7) *skater jump*; (8) Squat to front kick; (9) running; (10) *squat with front lunge*. Active recovery: Step-on	
Week 7–8		16 min 30 s 45 s HIIT work x 10 intervals + 60s active recovery x 9 intervals	HIIT work (10 movements) (1) *cross-punches*; (2) Squat twist; (3) Scissor jumps; (4) Squat to front kick; (5) *high knees*; (6) *high knees with touch*; (7) skater jump; (8) *side-step and prison squat*; (9) running; (10) squat with the front lunge. Active recovery: Step-on	
Week 9–10		17 min 20 s 50 s HIIT work x 10 intervals + 60 s active recovery x 9 intervals	HIIT work (10 movements) (1) cross-punches; (2) *in-out jump*; (3) *lunge jumps*; (4) squat to front kick; (5) high knees; (6) high knees with touch; (7) skater jump; (8) *lateral lunges*; (9) running; (10) *squat and uppercut*. Active recovery: Step-on	
Week 11–12		18 min 10 s 55 s HIIT work x 10 intervals + 60 s active recovery x 9 intervals	HIIT work (10 movements) (1) *lateral lunge and touchdowns*; (2) in-out jump; (3) lunge jumps; (4) squat to front kick; (5) *Heisman*; (6) high knees with touch; (7) *squat jump*; (8) fast running; (9) *low skater jumps*; (10) squat and uppercut. Active recovery: Step-on	
Week 13–14		19 min 60 s HIIT work x 10 intervals + 60 s active recovery x 9 intervals	HIIT work (10 movements) (1) *slams*; (2) side-step and prison squat; (3) squat jumps; (4) *lunge and knee drive*; (5) Heisman; (6) lateral lunges and touch down; (7) *reverse lunge*; (8) *seal jacks*; (9) fast running; (10) low skater jumps. Active recovery: Step-on	
Week 15–16		19 min 50 s 65 s HIIT work x 10 intervals + 60 s active recovery x 9 intervals	HIIT work (10 movements) (1) *lunge kick*; (2) side-step and prison squat; (3) squat with calf raise; (4) lunge and knee drive; (5) *twist jump*; (6) *slam and straight leg touch*; (7) butt kicks; (8) seal jacks; (9) low skater jumps; (10) *curtsy lunge.* Active recovery: Step-on	

HIIT, high-intensity interval training; HRmax, maximum heart rate; RPE, rate of perceived exertion.

The movement in italics indicates the new movement, which differs from the previous session.

A preparation session will be conducted at the research lab one month prior to the formal HIIT program. All participants in the HIIT group (*n* = 48) will initially have their HRmax estimated using an age-related prediction equation (54). Then, participants will be thoroughly familiarized with the 38 movements of the HIIT exercise and the entire HIIT procedure. Finally, participants will be asked to implement the HIIT program (30s HIIT work x 10 intervals + 60s active recovery x 9 intervals), where they will need to adjust their individual movement speed to reach the required HIIT intensity.

